## Abstract

**Background:**

Cisgender female sex workers (FSWs) experience high rates of HIV and sexually transmitted infections (STIs), including chlamydia and gonorrhea. Community empowerment–based responses to the risk environment of FSWs have been associated with significant reductions in HIV and STI risk and associated risk behaviors; however, evaluations of US-based interventions targeting FSWs are limited.

**Objective:**

The objective of this study is to describe the design, implementation, and planned evaluation strategy of an ongoing comprehensive community-level intervention in Baltimore City, Maryland, which aims to improve HIV and STI risk and cumulative incidence among FSWs. The two intervention components are the SPARC (Sex Workers Promoting Action, Risk Reduction, and Community Mobilization) drop-in center and the accompanying comprehensive mobile outreach program. The mission of SPARC is to provide low-barrier harm reduction services to FSWs, with a special focus on women who sell sex and use drugs. Services are provided through a harm reduction framework and include reproductive health and sexual health care; medication-assisted treatment; legal aid; counseling; showers, lockers, and laundry; and the distribution of harm reduction tools, including naloxone and sterile drug use supplies (eg, cookers, cotton, syringes, and pipes).

**Methods:**

The SPARC intervention is being evaluated through the EMERALD (Enabling Mobilization, Empowerment, Risk Reduction, and Lasting Dignity) study, which consists of a prospective 2-group comparative nonrandomized trial (n=385), a cross-sectional survey (n=100), and in-depth interviews assessing SPARC implementation (n=45). Participants enrolled in the nonrandomized trial completed a survey and HIV and STI testing at 4 intervals (baseline and 6, 12, and 18 months). Participants recruited from predefined areas closest to SPARC comprised the intervention group, and participants from all other areas of Baltimore were included in the control group.

**Results:**

We hypothesize that addressing structural drivers and more immediate medical needs, in combination with peer outreach, will improve the HIV and STI risk environment, leading to community empowerment, and reduce the HIV and STI cumulative incidence and behavioral risks of FSWs. Data collection is ongoing. A baseline description of the cohort is presented.

**Conclusions:**

In the United States, structural interventions aimed at reducing HIV and STIs among FSWs are scarce; to our knowledge, this is the first intervention of its kind in the United States. The results of the EMERALD study can be used to inform the development of future interventions targeting FSWs and other at-risk populations.

**Trial Registration:**

ClinicalTrials.gov NCT04413591; https://clinicaltrials.gov/ct2/show/NCT04413591.

**International Registered Report Identifier (IRRID):**

DERR1-10.2196/23412

## Introduction

### Background

Cisgender female sex workers (FSWs), defined as cisgender (ie, assigned female at birth and identifying as female) women who exchange sex for money, drugs, or goods, have 14 times the risk of being infected with HIV compared with those who do not exchange sex [1]. Similarly, cisgender FSWs experience sexually transmitted infections (STIs) at disproportionate rates [2-4]. Infectious diseases are often occupational hazards of sex work, with criminalization exacerbating HIV risk behaviors, including unprotected sex with multiple and high-risk sex partners [5,6]. The small body of research on HIV and STIs among FSWs in the United States finds high rates of HIV and STIs, similar to some other contexts globally [1,7,8].

The behavioral HIV and STI risk factors of FSWs are positioned in a broader context of enduring sociostructural vulnerabilities (eg, poverty, stigma, violence, and housing instability) that drive chronic substance use, victimization, and poor mental health, particularly in an illicit sex work market [9-11]. These factors are independently and synergistically associated with engagement in sex work and attendant HIV and STI risk [12,13] and are consistently found to be elevated among street-based and unsanctioned venue-based FSWs (eg, exotic dance clubs) compared with brothel-based FSWs [10,14,15]. The illegal nature of sex work heightens these vulnerabilities [10,14,15]. Substance use can also play a complex role in the lives of FSWs, with high rates being reported among samples of FSWs in a variety of settings [16-18]. Substance use can exacerbate engagement in risky sex and serve as a coping mechanism [19,20]. Sexual and physical abuse also heightens vulnerability to HIV and STI infection for FSWs [11,21,22]. Furthermore, FSWs have high rates of mental health morbidities (ie, depression and anxiety), which are risk factors for and underlying determinants of addiction and HIV and STI acquisition [23,24].

In response to these complicated needs and HIV and STI drivers, structural HIV and STI prevention interventions have been developed globally to address social, political, cultural, and economic factors that shape HIV and STI transmission [25-27]. Progress toward the global target of HIV elimination would not be possible without interventions and programs aimed at reducing high-risk behaviors among marginalized groups such as FSWs [28,29]. One of the most renowned and long-standing community-based structural interventions targeting FSWs, Sonagachi, addresses the burden of HIV among FSWs in Calcutta, India, with a holistic approach, including health clinics, banking cooperatives, and social services [30-32]. Using a community empowerment approach, Sonagachi prioritizes FSWs’ involvement in the implementation of the intervention, recognizes sex work as work, and operates from an understanding of the centrality of structural drivers in facilitating and mitigating the health of FSWs.

The Joint United Nations Programme on HIV and AIDS has recognized community empowerment in sex workers as the best practice for over a decade [33]. A recent meta-analysis found that community empowerment–based responses to HIV in FSWs were consistently associated with significant reductions in HIV, gonorrhea, chlamydia, syphilis, and increased condom use [34]. Although robust research exists in international settings, research on US structural interventions for FSWs is undeveloped [13,35,36]. A recent systematic review of US-based HIV and STI prevention intervention research with FSWs found that of 19 interventions, few were rigorously evaluated and none addressed the complex sociostructural context of risk [37].

The need for US-based interventions is underscored by results from our recently completed SAPPHIRE (Sex Workers and Police Promoting Health in Risky Environments) study, a prospective observational cohort study of cisgender (n=250) and transgender (n=63) street-based FSWs in Baltimore [38-46]. Cisgender FSWs showed elevated rates of structural vulnerabilities, including housing instability, food insecurity, limited education, and criminal justice involvement, and injection and noninjection drug use, compared with similarly aged peers. Structural vulnerabilities were associated with high baseline prevalence estimates of STIs, including HIV (5%), chlamydia (10%), and gonorrhea (12%) [40], and the incidence of chlamydia and gonorrhea was 13.7% and 18.2%, respectively, over 12 months [43]. Participants also reported frequent interactions with police and a high prevalence of police, intimate partner–, and client-perpetrated violence [38,44].

Building on these results, we aim to develop and evaluate the effectiveness of a community-based combination HIV and STI prevention intervention in Baltimore, Maryland, to include a range of biomedical (eg, HIV and STI testing and counseling, Title X–funded reproductive health, HIV treatment, drug treatment, and primary care referrals), behavioral (eg, HIV and STI risk reduction education), and structural (eg, financial literacy, legal aid, and housing referrals) services provided through SPARC (Sex Workers Promoting Action, Risk Reduction, and Community Mobilization), a drop-in center and comprehensive outreach program. This study uses a structural determinants framework (Figure 1) to understand the complex and multifaceted nature of FSWs’ HIV risk [47]. This framework is informed by fundamental cause theory, which argues that fundamental causes (eg, poverty) have a greater impact on health than behavioral risks, and empowerment theory, which links social participation to increased social cohesion [34,48,49]. In this paper, we describe the design of the EMERALD (Enabling Mobilization, Empowerment, Risk Reduction, and Lasting Dignity) study, which evaluates the impact of the SPARC intervention. We also detail the SPARC intervention aims, components, and lessons learned during implementation. All study procedures were approved by the Johns Hopkins Bloomberg School of Public Health Institutional Review Board (JHBSPH IRB).

**Figure 1 figure1:**
[figure not shown]
EMERALD (Enabling Mobilization, Empowerment, Risk Reduction, and Lasting Dignity) study theoretical framework. GED: general educational development; SPARC: Sex Workers Promoting Action, Risk Reduction, and Community Mobilization; STI: sexually transmitted infection; SW: sex worker.

### Aims and Hypotheses

The EMERALD study, detailed below, aims to examine (1) the effect of intervention exposure on HIV and STI risk behaviors (eg, drug use and unprotected sex) and HIV and STI cumulative incidence over time in FSWs in the intervention group compared with those in the comparison group, (2) how sociostructural (eg, social cohesion and stigma) and structural vulnerability (eg, financial and housing stability) indicators change and are associated with the biological and behavioral outcomes over time in FSWs in the intervention group compared with those in the comparison group, (3) the role of these indicators as mediators of the intervention effect on study outcomes, and (4) the implementation of the intervention through qualitative (eg, in-depth interviews) and quantitative (eg, assessment of program fit, reach, and cost, and facilitators and barriers to utilization measures).

The SPARC center and associated outreach is the intervention being evaluated by the EMERALD study, which consists of an 18-month longitudinal cohort study comprising intervention (n=224) and control (n=161) participants, a cross-sectional survey to assess program reach (n=100), and in-depth interviews (n=45) to assess SPARC implementation. We hypothesize that addressing structural drivers and more immediate medical needs, in combination with peer outreach, will lead to community empowerment and reduce FSWs’ HIV and STI incidence and behavioral risks.

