### Statistical Analysis

The principal analytic approach will center on generalized linear models for the individual data, with variance components that reflect the potential correlations among FSWs recruited from the same area and between repeated measurements from the same individual at baseline and follow-up visits [55,56]. The main covariate of interest is the intervention indicator. To address aim 1, we consider illicit drug use and irregular condom use as the primary behavioral endpoints.

The effect of the intervention will be assessed with a random effect hierarchical logistic model, with the intervention indicator, time, and their interaction as the main explanatory variables. To adjust for possible imbalances between the 2 areas, we will adjust for baseline confounding factors, including age, length of sex work, and number of sexual partners. The intervention effect will be assessed by comparing time trends in the intervention group with the time trend in the comparison group, as captured by the interaction term. The model will be expanded to include additional demographic covariates and time-dependent indicators of events such as arrest, homelessness, use of health services, or exposure to other prevention activities that are unrelated to the study. Aim 1 also seeks to evaluate the association between the degree of exposure to the intervention and observed behavioral changes. We will explore models that include as covariates participation or exposure to specific intervention components (ie, receiving medical care, drug treatment referral, and legal aid). On the basis of the literature, an 18-month follow-up should be sufficient to document meaningful changes in study outcomes, given the extent of the intervention [57].

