For the primary biological endpoint of HIV and STI incidence, we will initially estimate cumulative incidence rates in both the intervention and comparison participants as a binary outcome and construct confidence intervals, accounting for the correlation structure because of nesting in geographic recruitment areas. The intervention’s effect will be assessed using an unadjusted random effect logistic model, with the intervention indicator as the only explanatory variable. The model will be expanded to include baseline covariates, such as demographic characteristics, history of sex work, and baseline risk behaviors (ie, condom use). A more detailed analysis will employ person-time methods with Poisson regression models to allow for time-updated covariates measured over time. Those lost to follow-up will contribute time-at-risk until the time of their last visit.

Finally, to evaluate the reach of the intervention, we will estimate SPARC involvement of FSWs in the independent cross-sectional survey at the 18-month follow-up period. We will also compare this sample with the FSW cohort at 18 months to assess their comparability or differences regarding demographic and risk profiles using logistic regression with group membership as the outcome variable.

To address aim 2, we will first describe changes over time in various sociostructural (ie, social cohesion and stigma) and structural vulnerability (eg, housing stability) indicators. We will then contrast these trends between the intervention and comparison groups. Social cohesion, social participation, and collective action will be analyzed as aggregate measures, the form of which will be determined by exploratory analysis. Specific models for formal statistical comparisons will be developed based on exploratory analysis, identifying both the distributional properties of the indicators and the shape of changes over time. To assess the association of these changes with the study’s primary endpoints, we will develop random effects logistic models, where the changes in structural indicators at each visit compared with baseline will be the main explanatory factors, in addition to the intervention indicator. The random effects will reflect the nesting of observations within the recruitment area and person over time.

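### Aim 2, read literally, compares indicator–outcome associations between arms, but the stated association model fits one association common to both arms

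*Protocol article*

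**What the plan says.** **The aim.** Protocol article, Aims and Hypotheses: aim 2 concerns how the indicators listed there "change and are associated with the biological and behavioral outcomes over time in FSWs in the intervention group compared with those in the comparison" arm. The phrase naming the two groups follows both verbs.

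**The change part of the analysis.** Statistical Analysis first describes indicator changes over time, then states: "We will then contrast these trends between the intervention and comparison groups".

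**The association part.** The same paragraph continues: "To assess the association of these changes with the study’s primary endpoints, we will develop random effects logistic models". Their content is given as follows: "the changes in structural indicators at each visit compared with baseline will be the main explanatory factors, in addition to the intervention indicator". On the correlation structure: "The random effects will reflect the nesting of observations within the recruitment area and person over time".

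**The comparison with aim 1.** For the behavioural endpoints, the section describes a hierarchical logistic model "with the intervention indicator, time, and their interaction as the main explanatory variables". An interaction is named there. None is named for the aim 2 association model.

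**The concern.** A model with indicator change and arm as separate terms lets the arms differ in their overall level of risk. It does not let them differ in how strongly a change in, say, housing stability or social cohesion goes with the outcome. If aim 2 means what it literally says, that difference is one of the two things it sets out to examine, and the stated model contains no estimate of it.

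If the associations do differ between arms, the pooled coefficient is a mixture. It understates the association in one arm, overstates it in the other, and could hide opposite directions. A reader of the results would have no means of seeing this.

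**Working it through.** **1. Aim against model.** Write the stated model for one indicator, with random effects for area and woman:

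logit P(outcome) = a + b·change + c·arm + random effects.

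The log odds ratio per unit of change is b when arm = 0 and b when arm = 1. The term c shifts the level only. The stated random effects (area, person) add no arm-specific slope. Adding a product term gives

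logit P(outcome) = a + b·change + c·arm + d·(change × arm) + random effects.

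The association is now b in the comparison arm and b + d in the intervention arm, and d is the between-arm contrast. This step is algebra and needs no assumed figure.

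**2. What the pooled coefficient can hide (illustrations; all effect sizes assumed).**

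- *Single-level logistic data, 200,000 records.* Intervention share 160/272, binary indicator present in 40%, intercept −1.0, arm effect −0.2, true odds ratios 1.0 (comparison) and 0.5 (intervention). The additive model gives one odds ratio, 0.72. With the product term the estimates are 1.02 and 0.51.
- *Repeated measures.* 146 and 105 women (65% of 224 and 161), three follow-up visits, woman-level random intercept with SD 1, continuous indicator, fitted by logistic GEE, so odds ratios are population-average. With within-woman odds ratios per SD of 0.50 (intervention) and 1.00 (comparison), the pooled value is 0.73, against 0.56 and 1.01 by arm. With 0.60 and 1.20, the pooled value is 0.84, against 0.66 and 1.16.

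**3. Power for the interaction.** The article gives no power figure for aim 2. Its aim 1 figure (Cohort Study Target Population and Sample) serves to calibrate the effective sample size.

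- Inputs from the article: effective n of 160 and 112, rho = 0.2, three follow-up visits, 20% control prevalence, odds ratio 0.50, two-sided alpha 0.05.
- Multiplier for three correlated measures: 3 / (1 + 2 × 0.2) = 2.143, giving 342.9 and 240 effective observations.
- Intervention prevalence: 0.5 × 0.25 = 0.125 odds; 0.125 / 1.125 = 0.111.
- SE of the log odds ratio: √[1/(240 × 0.16) + 1/(342.9 × 0.0988)] = 0.236.
- Power: Φ(0.693/0.236 − 1.96) = 83.7%, which reproduces the stated 83%.

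For the interaction, with a binary indicator of prevalence q and an outcome of prevalence p, both taken as equal in the two arms (assumed):

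SE = √{ (1/240 + 1/342.9) × [1/q + 1/(1 − q)] / [p(1 − p)] }, with power Φ(0.693/SE − 1.96) for a ratio of odds ratios of 0.5.

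| p | q | SE | Power |
|---|---|---|---|
| 0.20 | 0.20 | 0.526 | 26% |
| 0.20 | 0.40 | 0.429 | 37% |
| 0.45 | 0.20 | 0.423 | 37% |
| 0.45 | 0.40 | 0.345 | 52% |

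With 65% of the 224 and 161 enrolled women instead of 160 and 112, the range is 24% to 49%.

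The repeated-measures illustration with 0.50 against 1.00 per SD detected the difference in 95% of runs, but it assumes a much larger effect. A binary indicator with 40% prevalence has SD √(0.4 × 0.6) = 0.49, so 0.50 per SD corresponds to 0.5^(1/0.49) = 0.24 for present against absent. The lower range is the safer guide.

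**The case against.** The strongest reply is that the aim is being read too strictly. Aim 1 closes with the same between-group phrase, and Statistical Analysis shows how the authors may have understood aim 2: describe change, contrast change between groups, then relate change to outcome with arm as an adjustment. On that reading, aim and model agree. This softens the point but does not remove it. The sentence as printed attaches the comparison to both verbs, so if the looser meaning is intended, the aim needs rewording.

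A second reply is that the model is not closed. The article says "Specific models for formal statistical comparisons will be developed based on exploratory analysis" and that fuller analysis details are available on request. An interaction may therefore be specified elsewhere. However, the flexibility sentence goes on to speak of the indicators' distributions and the shape of their changes, and it precedes the association model. The article then states that model's main terms, and they do not match the printed aim. The additive model is also not invalid: it estimates a legitimate pooled association, only not the comparison.

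Three stronger readings are tempting and are not supported:

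- *That all of aim 2 goes unanswered.* The change half is covered by the trend contrast.
- *That the study hypothesises associations holding only where SPARC operates.* The stated hypothesis is a pathway from intervention through empowerment to lower risk. It is compatible with an association common to both arms.
- *That aim 3 inherits this model.* The mediation analysis has its own framework, is described as initial and of limited power, and is not tied to the aim 2 specification.

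**Conclusion.** The point holds for the association half of aim 2. On the literal wording, that half is a between-arm comparison, and the model as described has no parameter for it. The conclusion rests on the wording of the aim and the named model terms, not on any simulation.

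The size of the consequence is unknown, because the documents give no association sizes. The odds ratios of 0.72 to 0.84 above only show what pooling would do if the arms differed as assumed. If they do not differ, the pooled estimate is adequate. No figure in the article is wrong and the primary comparisons are unaffected. It is worth correcting because a stated aim is involved and the correction is cheap.

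**What to change.** In the aim 2 association model in Statistical Analysis, add the product of indicator change and the intervention indicator, and include visit as a covariate, since the aim concerns association over time and indicator and outcome may drift together. Report the association in each arm with its confidence interval, and the contrast between them, labelled exploratory. Keep the pooled, arm-adjusted association alongside.

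Alternatively, if only a pooled association was intended, reword aim 2 so that the between-group comparison applies to change alone and the association is described as pooled and adjusted for arm.

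The cost is one product term per indicator, the visit term, and a line of text; no new data are needed. The price is wider intervals for the arm-specific associations and probably low power for the contrast, so a non-significant interaction should not be read as evidence that the associations are equal.

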## Methods

### Intervention: The SPARC Center and Outreach Program

The 2 intervention components are the SPARC drop-in center and the accompanying comprehensive outreach program, both of which target FSWs in the intervention area in south and southwest Baltimore (Figure 2). SPARC opened in November 2017, and the outreach program began in earnest the following fall. The mission of SPARC is to provide low-barrier harm reduction services to at-risk nonmen, with a special focus on women who sell sex and use drugs. SPARC addresses clients’ needs through nonjudgmental, convenient, safe, and nonstigmatizing interactions, reducing the need for outside referrals and increasing the likelihood of continued engagement in care and service utilization. All services are provided through a harm reduction framework, centering the lived experiences of those served, while addressing the structural and socioeconomic constraints that often limit their choices and options. Ultimately, SPARC’s overarching goal is to foster a sense of community and stimulate empowerment by creating a safe physical space in which women can connect and develop social cohesion and a sense of collectivism.

